#### Physical activity behaviours

Physical activity habits will be measured to assess the influence of this behaviour on body-composition changes. The pre-exercise screening system 2005 of Sports Medicine Australia will be employed to assess the participant's suitability to the particular level of physical activity before personalisation of the program [50]. A questionnaire to collect physical activity data will be prepared by adapting the International Physical Activity Questionnaire (IPAQ) [35,51] and will be administered by a trained researcher at baseline, 3 months and 6 months [35].

#### Depression, Anxiety and Stress Scale - 21 items (DASS 21)

The Depression, Anxiety and Stress Scale - 21 items (DASS 21) is a set of three self-reported scales designed to measure psychological health status [52]. Each of the three DASS 21 scales contains 7 items, divided into subscales with similar content. The Depression scale consists of items that assess dysphoria, hopelessness, devaluation of life, self-deprecation, lack of interest/involvement, anhedonia, and inertia. The Anxiety scale assesses autonomic arousal, skeletal muscle effects, situational anxiety and subjective experience of anxious affect. The Stress scale is sensitive to levels of chronic non-specific arousal. It assesses difficulty relaxing, nervous arousal, and being easily upset/agitated, irritable/over-reactive and impatient. Scores for Depression, Anxiety and Stress are calculated by summing the scores for the relevant items [34,38,52].

The DASS is a quantitative measure of distress, not a categorical measure of clinical diagnoses. However for clinical purposes it can be helpful to have 'labels' to characterise degree of severity relative to the population. Thus the cut-off scores have been developed for defining mild/moderate/severe/extremely severe scores for each DASS scale (Table 2).

**Table 2 T2:** DASS 21 recommended cut-off points [34]

	Depression	Anxiety	Stress
**Normal**	0-9	0-7	**0-14**
**Mild**	10-13	8-9	**15-18**
**Moderate**	14-20	10-14	**19-25**
**Severe**	21-27	15-19	**26-33**
**Extremely Severe**	**28+**	**20+**	**37+**

**Note**: the severity labels are used to describe the full range of scores in the population, so 'mild' for example means that the person is above the population mean but probably still below the typical severity of someone seeking help[34].

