Abdominal obesity has been suggested to be associated with overstimulation of the hypothalamic-pituitary-adrenal (HPA) axis [23,24] due to chronic stress [25], altering diurnal cortisol secretion. Abnormal regulation of the HPA axis and perceived stress-dependent cortisol levels are strongly related to perturbations of the endocrine axis as well as abdominal obesity with metabolic abnormalities [26].

A complex set of interrelationships occur between lifestyle, anthropometric, psychological and physical activity variables [27]. Of particular interest is the apparent relationship between physical and mental health [28,29]. Depressed people generally have lower physical activity levels than people without depression [30,31]. Lower physical activity levels also exacerbate depression resulting in a negative feedback cycle [32]. Conversely, increasing physical activity has the dual benefit of increasing physical fitness and alleviating depression and anxiety [29]. Even without the physical health benefits, increasing physical activity may block negative thoughts, distract people from worries, increase social contact and change the brain chemistry to improve mood [33]. Farming people are seldom thought of as being physically inactive, however the very nature of farming is seasonal, increasingly mechanised, with longer periods of being sedentary and greater reliance on vehicles. Further, opportunities for leisure time activity are reduced since many local sporting clubs have amalgamated or ceased to exist and access to a gymnasium or personal trainers is likely to be difficult due to distance and financial constraints.

The aim of this paper is to describe the pilot testing of the Farming Fit study which will examine the effect of physical activity on psychological health, obesity, impaired glucose tolerance, hypertension and dyslipidaemia in farm men and women.

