## Methods/Design

### Intervention community

Inclusion - Farm men and women participating in SFF programs will be recruited. Participants will be recruited from rural Victoria, have been farming for more than 5 years, be aged between 18 and 75 years, speak English and live 10 kilometres or more from a regional centre with a population greater than 10, 000. All study participants will be either overweight or obese as determined by body mass index (BMI) ≥ 25 kg/m^2^.

Exclusion - Participants will be excluded from the study if they have a chronic terminal illness or are pregnant or lactating mothers. People with very high levels of psychological distress will be referred for mental health assessment by a health professional (DASS 21 Score depression > 28 or anxiety > 20 or stress > 37) [33]. Subjects unable to participate in physical activity will not be eligible to participate.

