#### 3. Psychosocial assessment

A validated questionnaire, the 21-question depression, anxiety, stress score (DASS 21) will be used. The DASS 21 is made up of three seven item subscales covering depression, anxiety and stress as specified in Lovibonds and Lovibond [38].

Socio-demographic, health conditions and medication data will be collected from the participant including age, gender, country of origin, health care card using the Victorian Department of Health Service Coordination Tool Templates (SCTT) [39]. The type of farming undertaken and residential postcode will also be collected from participants.

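### DASS 21 scales are scored as seven-item sums with no stated conversion, but the referral triggers and Table 2 bands can all be reached by such a sum only if items run to at least 6

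*Protocol article*

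**What the plan says.** Two places in the protocol article give the structure of the instrument. Under Psychosocial assessment: "The DASS 21 is made up of three seven item subscales covering depression, anxiety and stress". In the DASS 21 section under Survey methodology: "Each of the three DASS 21 scales contains 7 items, divided into subscales with similar content".

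The DASS 21 section then gives the scoring rule: "Scores for Depression, Anxiety and Stress are calculated by summing the scores for the relevant items [34,38,52"]. No response range for an item, no maximum for a scale and no multiplier appears anywhere in the article.

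The same section introduces the severity bands: "Thus the cut-off scores have been developed for defining mild/moderate/severe/extremely severe scores for each DASS scale (Table 2"). The table is titled "DASS 21 recommended cut-off points [34"]. Its Extremely Severe band starts at 28 for depression, 20 for anxiety and 37 for stress.

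The exclusion paragraph under Intervention community uses the DASS as a safety screen: "People with very high levels of psychological distress will be referred for mental health assessment by a health professional". The criterion is "DASS 21 Score depression > 28 or anxiety > 20 or stress > 37) [33"].

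**The concern.** The article prints both a way to compute a score and thresholds to compare it with. The trigger uses the same three numbers as the top band of Table 2, so the two sets are evidently on one scale. Whether a sum of seven items is on that scale depends on the item range, which is not given. For most small item ranges it is not: some thresholds lie above the largest possible sum.

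What is at stake is the referral of very distressed people. The article motivates the study by high suicide rates in farming communities, and this trigger is the only numeric distress safeguard it describes. If the sum is compared directly with numbers meant for a larger scale, the error is silent and runs towards under-referral. Severity labels would be too mild for the same reason.

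The citation at the trigger gives minor support. It points to reference [33], which the Background cites for the claim that activity may "distract people from worries, increase social contact and change the brain chemistry to improve mood [33"]. The DASS, and the cut-offs in Table 2, are attributed elsewhere to [34]. A reader who starts at the trigger is not led to the scoring source.

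**Working it through.** **Inputs.** Seven items per scale (Psychosocial assessment; DASS 21 section). Score = sum of items (DASS 21 section). Triggers > 28, > 20, > 37 (Intervention community). Table 2 bands. The lowest band of Table 2 starts at 0, so under a plain sum items are taken as whole numbers starting at 0. The article states no item or scale maximum, so there is no figure of its own to reproduce. The item maximum *m* is an assumption and is varied from 3 to 6.

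**Step 1: mean item score that must be exceeded.** Trigger / 7:
- depression 28/7 = 4.00
- anxiety 20/7 = 2.86
- stress 37/7 = 5.29

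**Step 2: smallest item maximum that reaches each trigger.** The lowest whole scores that trigger are 29, 21 and 38. Divide by 7 and round up:
- depression 29/7 = 4.14, so *m* ≥ 5
- anxiety 21/7 = 3.00, so *m* ≥ 3
- stress 38/7 = 5.43, so *m* ≥ 6

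For the Table 2 top band (28, 20, 37) the same step gives 4, 3 and 6. Stress is the binding scale in both cases.

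**Step 3: what can be reached for each item maximum.** Largest sum = 7*m*.

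| *m* | Largest sum | Depression > 28 | Anxiety > 20 | Stress > 37 | Highest Table 2 label (depression / anxiety / stress) |
|---|---|---|---|---|---|
| 3 | 21 | never | 21 only | never | Severe / Extremely Severe / Moderate |
| 4 | 28 | never | 21–28 | never | Extremely Severe / Extremely Severe / Severe |
| 5 | 35 | 29–35 | 21–35 | never | Extremely Severe / Extremely Severe / Severe |
| 6 | 42 | 29–42 | 21–42 | 38–42 | Extremely Severe on all three |

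At *m* = 5 the largest stress sum, 35, falls between the printed bands 26–33 and 37+, so the highest label reached is Severe. That gap at 34–36 is a separate matter.

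**Step 4: what a conversion would do.** Assume items 0–3 and a doubled sum. The largest score is 2 × 21 = 42, and every threshold can be reached. With *S* the undoubled sum, the triggers become:
- 2*S* > 28, so *S* ≥ 15
- 2*S* > 20, so *S* ≥ 11
- 2*S* > 37, so *S* ≥ 19

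If the Table 2 floors (28+, 20+, 37+) are meant instead, they become *S* ≥ 14, 10 and 19. Under the same two assumptions, undoubled sums of 14, 10 and 19 should read as 28, 20 and 38, all Extremely Severe. Compared directly with Table 2, all three read as Moderate.

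**Step 5: effect on the planned tests.** If every DASS score is multiplied by the same constant, means, differences and standard errors scale together, so test statistics and p-values for continuous scores do not change. The article specifies no categorical DASS analysis.

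**The case against.** The strongest reply is that the document contains no proven contradiction. The rule and the thresholds clash only if items run below 6, and the article does not give the item range. With items up to 6 everything can be reached. Response options and conversion for a published questionnaire are details that a condensed article may leave to the manual. The scoring sentence cites three sources, and Table 2 takes its cut-offs from one of them, so staff who follow that source for both would be consistent. Trained research staff carry out the assessments, and the [33] at the trigger may be only a numbering slip.

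Much of this stands. The item range is unknown from the document, correct scoring may already be in place, and the citation point shows little on its own. What does not stand is the view that this is only missing detail. The article itself prints a summing rule and a numeric safety trigger, and a reader who applies the one to the other as written gets a referral that works on all three scales only for items reaching 6.

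A reader might infer more: that the depression and stress referrals cannot fire in this trial, or that the DASS results will be wrong. The documents support neither. The first needs both an item range below 5 and scoring without the conversion, and neither is documented. The second fails because a constant multiplier leaves tests on continuous scores unchanged.

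**Conclusion.** The point holds as a conditional defect in safety referral and severity labelling. Scored as printed, the stress referral cannot fire for any item maximum below 6, and the depression referral cannot fire below 5. At an item maximum of 3, anxiety fires only at the top score of 21. This rests on whole-number items starting at 0, on a plain sum, and on an item maximum that the article does not state.

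If staff score by the cited sources, the effect may be nil. The planned tests on continuous DASS scores are not affected under a constant multiplier. The article gives no distribution of DASS scores, so the number of people who might be missed cannot be estimated. It should be fixed because the safeguard protects distressed people and the correction is small. Confidence is medium, since the item range and the cited scoring instructions are not visible.

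**What to change.** After checking the cited manual, do one of the following:
- In the DASS 21 section, state the item range and the conversion that puts the seven-item sum on the Table 2 scale. If items are 0–3, this is doubling, with a maximum of 42.
- Restate the triggers under Intervention community on the summed scale. If items are 0–3 and doubling applies, these are depression ≥ 15, anxiety ≥ 11 and stress ≥ 19 when the strict inequality is kept, or ≥ 14, ≥ 10 and ≥ 19 when the Table 2 floors are meant.

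In either case, cite the scoring source at the trigger and confirm that the screening form uses the same scale as the thresholds. The cost is one sentence, one citation and one check of a form. The downside is that more people may be flagged for referral.

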#### Data entry, handling and statistical analysis

Data will be tabulated and analysed using PASW^® ^statistics 18 software. Variables will be reported as means with 95% confidence intervals. Repeated measures ANOVA, paired sample t-tests, multiple linear regression, and binary logistic regression will be used to test for intervention effects after adjusting for relevant co-variables (e.g. sex, age) and baseline scores. Since physical activity scores are likely to reflect a non-normal distribution, comparisons between the sexes at baseline and over time will be performed using the Kruskal-Wallis test. Linear regression analysis will be used to assess the association between body fat percentage, body mass index and cortisol levels. Correlation coefficients between body composition, physical activity, and metabolic variables will be calculated using Pearson's and Spearman's correlation as appropriate. P values will be considered statistically significant at P < 0.05.

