### Study design

This is a 6-month quasi-experimental control intervention study. Intervention and control group participants whom fulfil the abovementioned criteria will be selected from SFF programs. SFF program groups (clusters) will be randomly assigned to control and intervention groups with participants from each cluster being assigned to the same group to minimise the contamination effect.

The proposed intervention includes:

**1**. An individualised exercise coaching program for the intervention group designed by an exercise physiologist and undertaken over the entire 6-month period.

**2**. An exercise physiologist/research assistant to provide consultation on individualized exercise programs and coach over the 6-month period.

**3**. Regular monitoring of exercise activity and exercise goals by phone, email and/or mobile text message.

Participant's anthropometric and basic physical assessments and psychological assessments (DASS 21 scores) will be measured. Venous blood samples following a 10-hour fast will be taken for biochemical analysis of lipids, glucose and cortisol levels. Salivary cortisol measurements will be taken. Diet and physical activity data will be obtained using self reported questionnaires based on previously developed instruments [35,36]. Data collection will be repeated following completion of the 6-month intervention.

Diet and physical activity questionnaires and salivary cortisol samples are to be repeated following an interim 3-month period of the proposed study as outlined in Table 1. Participants from the intervention group will receive a personalised exercise program and regular phone coaching in order to promote increased physical activity.

**Table 1 T1:** Data collection and timeline for both intervention and control groups

Variable	Base line	3 month	6 month
Body weight (kg)	✓	**X**	✓
Height (cm)	✓	**X**	✓
Waist circumference (cm)	✓	**X**	✓
Hip circumference (cm)	✓	**X**	✓
Body fat (%)	✓	**X**	✓
Blood pressure (mmHg)	✓	**X**	✓
Pulse rate (bpm)	✓	**X**	✓
Fasting blood glucose (mmol/L)	✓	**X**	✓
Fasting blood cholesterol (mmol/L)	✓	**X**	✓
Fasting triglycerides (mmol/L)	✓	**X**	✓
HDL (mmol/L)	✓	**X**	✓
LDL (mmol/L)	✓	**X**	✓
Fasting blood cortisol (nmol/L)	✓	**X**	✓
Salivary cortisol*(nmol/L)	✓	✓	✓
DASS score	✓	✓	✓
Dietary questionnaire	✓	✓	✓
Physical activity questionnaire	✓	✓	✓

* Salivary cortisol will be measured by taking 4 readings/day (9 am, 12 pm, 4 pm and 8 pm)

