### Sample size

To evaluate the intervention, sample size was determined at the power of 80% (β = 0.2) with α set at 0.05 for an effect size of a standard deviation change of fasting serum cortisol and/or a 0.5 standard deviation reduction of body weight by the end of the intervention. This required the sample size to be a minimum of 64 participants across the control and intervention groups [37]. By considering the probable retention rate (≥95%) for a 6-month intervention the target recruitment number was fixed at a minimum of 35 participants in both the control and intervention groups, requiring recruitment of a total of 70 farming participants meeting the above criteria.

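### Repeated measures ANOVA discards participants who miss only the 3-month visit on the three-visit outcomes; a mixed model in the same software would keep them

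*Protocol article*

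**What the plan says.** The section on data entry, handling and statistical analysis, which names PASW statistics 18 as the software, states: "Repeated measures ANOVA, paired sample t-tests, multiple linear regression, and binary logistic regression will be used to test for intervention effects", and continues "after adjusting for relevant co-variables (e.g. sex, age) and baseline scores". No method is tied to a particular outcome, and the adjustment phrase covers all four methods.

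The schedule is in Table 1 under Study design ("Data collection and timeline for both intervention and control groups"). Of its 17 rows, 13 are ticked at baseline and 6 months only. These include body weight and fasting blood cortisol, the two outcomes used in the Sample size section. The other four rows (salivary cortisol, DASS, dietary questionnaire, physical activity questionnaire) are ticked at all three visits. Saliva is taken four times on each sampling day. The running text under Study design does not mention DASS among the 3-month repeats; Table 1 does, and I follow Table 1.

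The section on impact and outcome evaluation describes analysing 3- and 6-month data with adjustment for baseline. The Sample size section allows for dropout thus: "By considering the probable retention rate (≥95%) for a 6-month intervention". That leads to 35 participants per group, 70 in total.

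**The concern.** Classical repeated measures ANOVA works on a full vector of responses per participant. If one visit is missing, the whole participant leaves the analysis. For the three-visit outcomes this happens whether baseline is a response (three values needed) or only a covariate with 3 and 6 months as responses (still three values needed). Someone who stayed to the end and supplied a 6-month DASS score is lost because of one missed interim questionnaire. In a trial of 70 each such loss counts, and DASS measures psychological distress, which is central to the study's aim. If missing the interim visit is related to outcome, the contrast could also be biased; the article gives no information on whether it is.

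The two-visit outcomes raise a different question. With one post-baseline value, a repeated measures ANOVA has nothing to repeat unless baseline is itself a response. Under the stated adjustment, baseline would then stand on both sides of the model. What needs checking is whether that damages the test, the estimate, or both.

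**Working it through.** **Inputs from the article.** Recruitment 70, retention 95%, alpha 0.05 (two-sided assumed), 1:1 allocation, visits from Table 1.

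**Assumed inputs.** Share of retained participants missing 3 months: 5%, 10%, 15%. Saliva samples missing: 1%, 2%, 5%, independently. Effect for illustration: 0.7 SD, chosen because it gives about 80% power at the expected number with 6-month data. Clustering by SFF group is ignored throughout.

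**The plan's own figure.** The Sample size section aims at 80% power with alpha 0.05. Its two target effects are 1 SD for fasting cortisol and 0.5 SD for weight, and it arrives at "a minimum of 64 participants across the control and intervention groups". The two-sample formula n = 2(1.96 + 0.84)²/d² gives 63 per arm for d = 0.5 (64 with the t distribution) and 16 (17) for d = 1. So 64 matches the per-arm number for 0.5 SD, not a total. That is a separate matter. Here I use only the recruitment target of 70, which is close to 64/0.95 = 67.4, i.e. 68.

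**Three-visit outcomes: complete cases.** Expected number with 6-month data: 70 × 0.95 = 66.5. Complete cases = 66.5 × (1 − q); power by two-sample t-test with half in each arm.

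| Miss 3 months, q (assumed) | Complete cases | Dropped despite 6-month data | Power, 0.7 SD |
|---|---|---|---|
| 0 | 66.5 | 0 | 80% |
| 5% | 63.2 | 3.3 | 78% |
| 10% | 59.9 | 6.7 | 76% |
| 15% | 56.5 | 10.0 | 73% |

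**Salivary cortisol, worst case.** Four samples at three visits make 12 values. If all 12 were entered as separate factor levels, the share incomplete is 1 − (1 − s)^12: 11% at s = 1%, 22% at 2%, 46% at 5%. Of 66.5, about 59, 52 or 36 would remain. A daily summary would lose fewer, depending on how partly missing days are handled.

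**Two-visit outcomes: who is dropped.** Repeated measures ANOVA and regression of the 6-month value on baseline need the same two values, so both use the same participants. There is no extra loss.

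**Two-visit outcomes: the test.** Let b be baseline and y the 6-month value, with arm and b as regressors.

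- ANCOVA: response y; arm coefficient β, standard error s.
- Time-by-group test: response y − b. Subtracting b changes only the coefficient of b, so the arm coefficient and standard error remain β and s.
- Group main effect: response (y + b)/2. Adding b again changes only its own coefficient; halving gives β/2 and s/2.

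All three have t = β/s and the same p-value. A simulation with 33 per arm (2,000 data sets, no true effect, baseline correlation 0.7) confirmed this: the largest p-value difference was 8 × 10⁻¹⁵, and the type I error was 0.0475 for all three. In one data set with an effect, the estimates were 0.66, 0.66 and 0.33, each with t = 3.83.

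**The case against.** The strongest reply is that the article does not assign repeated measures ANOVA to any particular outcome. Baseline-adjusted multiple linear regression stands in the same sentence and suits the two-visit outcomes. The section on impact and outcome evaluation, with 3- and 6-month data adjusted for baseline, allows a model in which baseline is only a covariate. Matching methods to outcomes and setting out missing-data handling are commonly left to a full protocol or SAP. This stands: it disposes of any claim that weight or fasting cortisol will be wrongly tested, and the absence of such detail is not the point made here. It does not remove the complete-case loss, because repeated measures ANOVA is a named method and drops incomplete participants under either role for baseline.

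A reader might infer that using it on weight or cortisol would cost most of the power, since the group main effect averages in a visit where no effect exists. For 0.5 SD with 33 per arm, that main effect has 18-21% power, against 64% to over 99% for ANCOVA at baseline correlations of 0.5-0.9. But the low figures hold only without baseline as covariate, and the article adjusts for baseline. Even unadjusted, the natural test would be the group-by-time interaction, with 52%, 73% and 99% power at correlations of 0.5, 0.7 and 0.9.

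A reader might also infer that those dropped are the less adherent. The article offers nothing to support that. Finally, the loss is small if few miss 3 months, and the large saliva losses require a 12-level model that the article does not describe. Both are fair limits on the size of the point.

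**Conclusion.** The point holds for the four three-visit outcomes and is modest in size. Under an assumed 5-15% missing at 3 months among those retained, 3 to 10 of about 66 participants with 6-month data are discarded, costing about 2-7 percentage points of power for an illustrative 0.7 SD effect. The article states no effect size for these outcomes: its 1 SD and 0.5 SD refer to fasting cortisol and body weight. The 95% retention figure does not settle the matter, since it concerns staying in for six months, not attending the interim visit. Salivary cortisol could lose more, but only if all 12 samples are modelled separately.

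For the two-visit outcomes there is no extra loss of participants, power or type I error control under the stated baseline adjustment. One narrower risk remains. If repeated measures ANOVA were used there and its group main effect reported as the treatment effect, the estimate would be half the 6-month difference. To call the method invalid for the whole schedule would go further than the document supports.

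**What to change.** For DASS, diet, physical activity and salivary cortisol, replace repeated measures ANOVA with a linear mixed model (MIXED in PASW): 3- and 6-month values as responses, baseline as covariate, arm by visit, and random effects for participant and for SFF group, since whole groups are assigned. Keep all observed values and take the 6-month arm contrast as the test.

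For outcomes measured at baseline and 6 months only, state that the linear regression already listed will be used, with the 6-month value regressed on arm and baseline, accounting for SFF group.

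The cost is a change of wording and slightly more analysis work, with no change to data collection. The mixed model relies on data being missing at random given what is observed, and the text should say so.

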### Impact and outcome evaluation

Impact and outcome evaluation will be achieved by assessing the immediate and longer term effects of the program. Differences in individual and group impacts and outcomes will be measured using longitudinal (3- and 6-month) data with adjustment for baseline data to evaluate any significant changes across the period of the study. The impact outcome of the anthropometric, biochemical and psychological variables of the intervention will be measured using the quasi-experimental study. Differences between intervention and control groups will be statistically ascertained.

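### Paired t-tests are listed as tests of the intervention effect, but they measure change within one group, ignore the controls and cannot take the stated adjustment

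*Protocol article*

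**What the plan says.** Under *Data entry, handling and statistical analysis*, the article gives one list of methods a single purpose. After naming repeated measures ANOVA it continues: "paired sample t-tests, multiple linear regression, and binary logistic regression will be used to test for intervention effects after adjusting for relevant co-variables". The covariates given as examples are sex and age, and baseline scores are added. The section sets the threshold: "P values will be considered statistically significant at P < 0.05". Nothing there limits the paired test to describing change within a group.

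Elsewhere the target is a contrast between groups. *Impact and outcome evaluation* states: "Differences between intervention and control groups will be statistically ascertained", and it also calls for adjustment for baseline data. The Methods paragraph of the Abstract likewise describes a longitudinal comparison of intervention with control.

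Under *Study design*, whole Sustainable Farm Families (SFF) program groups are assigned to one condition or the other. No matching of individual participants across conditions is described.

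**The concern.** Participants are not matched across groups, so the only pairs available are a participant's own time points. A paired t-test on those pairs asks whether the mean change in one group differs from zero. Three things follow.

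- It uses no control data, so it cannot separate the effect of coaching from anything that moves both groups.
- It has no place for sex, age or baseline as covariates, so the sentence asks of it something it cannot do.
- Its estimand is not the between-group difference that the article names as its aim.

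Common change is plausible here. The *Background* says that "the very nature of farming is seasonal", follow-up lasts 6 months, and both groups come from the SFF program, which may itself change behaviour. A concurrent control group is there to remove such change, and the paired test discards it. If the listed method is applied as written, drift in both groups could be reported as an intervention effect.

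**Working it through.** The article gives no figure for this point, so there is none to reproduce. The check shows how the test behaves when the intervention does nothing.

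**Inputs**
- Completers per group: 35 recruited (*Sample size*) × 0.95 retention (*Sample size*) = 33.25, taken as 33.
- Significance level: 0.05 from the article. Two-sided testing is an assumption, because sidedness is not stated.
- True intervention effect: none.
- Common shift in both groups: *d*, in SD of change. This is assumed, because the article gives no drift for any outcome.

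**Paired test in the intervention group.** The test statistic has 32 degrees of freedom, a critical value of 2.037 and noncentrality *d* × √33, where √33 = 5.745.

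| Common shift *d* | Noncentrality | Paired test significant | Between-group test of change significant |
|---|---|---|---|
| 0 | 0 | 5% | 5% |
| 0.2 | 1.149 | 20% | 5% |
| 0.3 | 1.723 | 39% | 5% |
| 0.4 | 2.298 | 61% | 5% |

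A simulation of 20,000 trials per setting gives the same percentages for the three shifts. The between-group test holds its level because the common shift cancels in the difference between groups.

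**Sensitivity to scale.** If drift is expressed in SD of the outcome, the SD of change is √(2(1 − ρ)) outcome SDs, where ρ is the baseline-to-follow-up correlation (assumed). At ρ = 0.7 that is √0.6 = 0.775, so a drift of 0.2 outcome SD equals 0.2/0.775 = 0.258 SD of change. Simulated with 32 per group at ρ = 0.7, the paired test is significant in 11% of trials at a drift of 0.1 outcome SD, 30% at 0.2 and 56% at 0.3. At a drift of 0.2 it is 20% for ρ = 0.5 and 69% for ρ = 0.9. Over drifts of 0 to 0.5 SD, with 32 or 35 per group, the between-group test stays between 4.7% and 5.4%.

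**Regression to the mean.** Entry requires BMI of at least 25. Suppose the share of overweight or obese farmers in the *Background* (64.3%) applies to the source population and values are normal. The mean of those selected then lies 0.58 SD above the population mean, and the expected fall at remeasurement is (1 − reliability) × 0.58:
- reliability 0.98: 0.02 × 0.58 = 0.01 SD
- reliability 0.90: 0.10 × 0.58 = 0.06 SD

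This is small, so the argument rests on other change common to both groups.

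**Clustering.** The 5% for the between-group test assumes independent participants. With an assumed 10 per program group, the design effect is 1 + 9 × ICC. At ICC 0.02 it is 1.18, and 1.96/√1.18 = 1.80 gives about 7% error. At ICC 0.05 it is 1.45, and 1.96/√1.45 = 1.63 gives about 10%.

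**The case against.** The strongest reply is that the article already names valid analyses. The same sentence lists repeated measures ANOVA, which can carry a group-by-time term, and linear regression adjusted for baseline, sex and age. *Impact and outcome evaluation* and the Abstract both point to a comparison between groups. This stands, and it narrows the point: the plan has a sound test, and the error is to give the paired test the same role.

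A second reply is that the drift is assumed. This also stands. The remark on seasonality concerns farm work and physical activity, not weight, cortisol or DASS scores. No calendar dates are given, so it is not established that baseline and final visits fall in opposite seasons, and staggered entry would cancel part of any seasonal change. With no drift the paired test keeps its 5%.

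Some stronger readings are tempting, but the documents do not support them.

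- *Significance in the intervention group alongside non-significance in the control group will be taken as proof of effect.* The article states no such rule. The wording leaves room for it but does not adopt it.
- *There are four competing tests for every outcome, with no order among them.* The list covers many variables, and logistic regression is for binary outcomes, so it is no alternative for weight or cortisol. Which method serves which outcome, and in what order, is commonly settled in an analysis plan that is not shown.
- *Regression to the mean from the BMI criterion is a major bias.* For reliably measured weight it is small, as shown above, and no minimum DASS score is required for entry.
- *The sample size shows that a paired test is the main analysis.* The article requires "a minimum of 64 participants across the control and intervention groups". A within-group formula at 0.5 SD gives ((1.96 + 0.84)/0.5)² = 31.4, or 32 per group and 64 in all. But 64 is also the t-based number per group for a between-group difference of 0.5 SD, so it could be a per-group figure written as a total. The article does not say which.

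**Conclusion.** The point holds in a limited form. As written, the article assigns paired t-tests a task they cannot perform: they neither use the control group nor adjust for covariates, and they do not estimate the between-group difference that the article sets out to measure. This follows from the wording and the design and needs no assumption.

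The size of the consequence does rest on assumptions. With 33 per group, two-sided testing at 0.05 and a common shift of 0.2 to 0.4 SD of change, the intervention-group paired test gives a false positive in about 20% to 61% of trials, against about 5% for a between-group test with clustering ignored. These figures illustrate the mechanism and do not forecast this trial. The paired test *could* credit common change to the intervention; the documents do not show that it will. A reader might infer that the plan has no valid test of the effect, but the baseline-adjusted methods in the same sentence show otherwise.

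**What to change.** Reword the analysis section so that, for continuous outcomes, the only test of the intervention effect is the between-group, baseline-adjusted comparison already named there. This can be either of:
- regression of the 6-month value on group, with baseline value, sex and age as covariates; or
- the group-by-time term of the repeated measures ANOVA.

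Either should allow for SFF program group as the unit of assignment. The number of program groups is not given, so the way to do this (a random effect, for example) has to be chosen once it is known. Report the adjusted difference between groups with its 95% confidence interval.

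Move paired t-tests to a separate sentence that limits them to describing change within each group, with no claim about the intervention.

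The change needs no further participants, visits or measurements. Its cost is that significant within-group results can no longer be presented as intervention effects.
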